### Provisions for post-trial care {30}

There is no post-trial care scheduled.

### Outcomes {12}

#### Primary outcome

The decline ratio of serum AMH levels 12 weeks after surgery: the decline ratio of serum AMH levels is defined as the value of (preoperative AMH levels − postoperative AMH levels)/(preoperative AMH levels). Serum AMH levels will be quantitatively measured by using an enzyme-linked immunosorbent assay.

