## Methods: participants, interventions, and outcomes

### Study setting {9}

As a multi-center trial, the study will be conducted at Seoul National University Hospital and Dongguk University Ilsan Hospital, in the Republic of Korea. All participants will be randomly assigned with a 1:1 ratio from the two hospitals.

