### Sample size {14}

The number of participants is determined on the basis of the decline ratio of serum AMH levels 3 months after surgery with a significance level of 2.5% and the test power of 80%. For patients with ovarian EMS treated with laparoscopic suturing, the decline ratio of serum AMH levels 3 months after surgery has been reported to be 24.6% (interquartile range [IQR], 11.6–37.0) in the previous study [14]. From IQR and with the assumption of a normal distribution, standard deviation (SD) was calculated to be 18.81, where SD = IQR/1.349. Although the information on confidence intervals from relevant trials is required for determining the non-inferior margin, there appears no available study for confidence intervals. In one study on the comparison of the preservation of ovarian reserve between hemostatic suturing and electrocoagulation, it was reported that there was no significant difference between the two groups with respect to a reduction rate of serum AMH 3 months after surgery (suturing group 44% ± 28% vs. electrocauterization group 58% ± 24%, *p* = 0.15) [15]. Based on the 14% difference in the rate, we have calculated appropriate numbers of participants for the non-inferior margin from 8 to 14%. The smaller the non-inferior margin, the larger the sample size. Therefore, we set the non-inferior margin at 12% for the primary outcome, which will not be applied for the secondary outcomes because of a lack of relevant references. For the statistical test on non-inferiority with a mean difference of 0, the value for the sample size (*n* = 80) is available with SD of 18.81, and a non-inferior margin of 12% between the two groups, suggesting that the number of participants of each group is estimated to be 40. Supposed that the dropout rate is 10%, the number of participants should be 90 (45 per group).

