## Statistical methods

### Statistical methods for primary and secondary outcomes {20a}

Both per-protocol (PP) and intention-to-treat (ITT) populations will be analyzed in two groups. The result will be regarded as valid when the experimental group is not inferior to the control group for the primary outcome, preservation of the ovarian reserve, in both analyzing methods. Serum AMH levels will be analyzed by using the Student *t* or Mann-Whitney *U* tests and repeated measure ANOVA. For secondary endpoints, variables will be analyzed by using the chi-square or Fisher’s exact test for categorical data and the Student *t* or Mann-Whitney *U* test for numerical data. *p* value < 0.05 is considered statistically significant.

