### Methods for additional analyses (e.g., subgroup analyses) {20b}

A separate supporting analysis will be conducted for unilateral or bilateral ovarian EMS.

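### The AMH decline ratio has no lower bound and entry starts at 0.05 ng/ml, so one low-baseline patient can cost power; the named tests make little use of known covariates

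*Protocol article*

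**What the plan says.** Under Primary outcome, "the decline ratio of serum AMH levels is defined as the value of" "preoperative AMH levels − postoperative AMH levels)/(preoperative AMH levels", calculated for each patient at 12 weeks. The inclusion criteria admit a serum AMH as low as 0.05 ng/ml.

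The statistical methods section {20a} states: "Serum AMH levels will be analyzed by using the Student *t* or Mann-Whitney *U* tests and repeated measure ANOVA". It names no covariate and gives no rule for choosing between the t test and the Mann-Whitney test. Laterality appears only in section {20b}: "A separate supporting analysis will be conducted for unilateral or bilateral ovarian EMS". On hospitals, the study setting section says "All participants will be randomly assigned with a 1:1 ratio from the two hospitals", and the recruitment section allows more institutions to join.

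The sample size section works on a difference in mean decline with a 12-point margin and a true difference of 0, "with a significance level of 2.5% and the test power of 80"%. The control decline "has been reported to be 24.6% (interquartile range [IQR], 11.6–37.0"), and the "standard deviation (SD) was calculated to be 18.81, where SD = IQR/1.349", assuming normality. The result is 40 evaluable patients per group, or 45 with 10% dropout.

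**The concern.** Two separate features of the plan reduce the chance of a clear answer.

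1. **The scale.** Dividing by a denominator that may be as small as 0.05 ng/ml turns a small absolute rise into a decline of −100% or −200%. The planning SD comes from an interquartile range under normality, and an interquartile range carries no information about that tail.
2. **Unused information.** Baseline AMH, laterality and hospital are known for every patient. The protocol thinks laterality important enough for its own analysis, yet the tests named for AMH do not use it.

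The trial is sized for 80% power with nothing in hand, so extra variance moves the upper confidence limit towards or past 12 points even when the two methods are equivalent.

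**Working it through.** **Inputs from the protocol article.** Margin 12 points, SD 18.81, true difference 0, one-sided 2.5% (the stated level is read as one-sided), 80% power, 40 evaluable per arm, control decline 24.6%, lowest baseline 0.05 ng/ml.

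**Assumed inputs, not in the article.** The share of variance explained by the covariates (R²), the distribution of baseline AMH, and assay error.

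**1. The plan's own figure.** Normal approximation: n = 2 × (1.96 + 0.842)² × 18.81² / 12² = 38.6, so 39 per arm. With the noncentral t distribution it is 40 per arm (power 80.4%). 40 / 0.9 = 44.4, so 45 per arm and 90 in all. The stated sample size reproduces. (25.4 / 1.349 is 18.83, not 18.81; this does not matter.)

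**2. One patient in an arm of 40.** Let the other 39 average 24.6%. A patient with decline d shifts the mean by (d − 24.6)/40, and the arm SD becomes √{[38 × 18.81² + (d − 24.6)² × 39/40] / 39}.

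| Baseline to 12 weeks (ng/ml) | Decline d | Shift in arm mean | Arm SD |
|---|---|---|---|
| 0.05 to 0.10 | −100% | −3.1 points (26% of margin) | 27.1 |
| 0.05 to 0.15 | −200% | −5.6 points (47% of margin) | 40.1 |
| 3.0 to 3.1 | −3.3% | −0.7 points | 19.1 |

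**3. Effect on the decision quantity.** Upper 95% limit for experimental minus control decline = difference + 1.99 × √[(SD₁² + SD₂²)/40], with both arms otherwise at 24.6%.

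- No such patient: 0 + 1.99 × 4.21 = 8.4.
- One −100% patient in the control arm: 3.1 + 1.99 × 5.21 = 13.5, so non-inferiority is missed. In the experimental arm: −3.1 + 10.4 = 7.3.
- One −200% patient in the control arm: 5.6 + 1.99 × 7.00 = 19.5. In the experimental arm: −5.6 + 13.9 = 8.3.

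**4. What adjustment gains.** Residual SD = 18.81 × √(1 − R²), three covariate degrees of freedom, 40 per arm.

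| R² (assumed) | Residual SD | Power |
|---|---|---|
| 0 | 18.81 | 80.4% (about 0.04 points below unadjusted) |
| 0.05 | 18.33 | 82.4% |
| 0.10 | 17.84 | 84.3% |
| 0.20 | 16.82 | 88.3% |
| 0.30 | 15.74 | 92.0% |

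Adjustment breaks even at an R² of about 0.0015.

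**5. Does adjustment repair the tail?** This was simulated with lognormal baseline AMH, declines of 24.6% ± 18.81 in both arms and additive assay error. Without assay error, power stays near 80%. With an error SD of 0.1 ng/ml, unadjusted power is about 72% (median baseline 3 ng/ml, log-SD 0.7), 68% (median 3, log-SD 1.0) or 58% (median 2, log-SD 1.0). Adding log baseline AMH to the model changed power by less than 2 points in every scenario. It does not repair the tail.

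**6. The margin on a log scale.** A 12-point larger loss than 24.6% is a loss of 36.6%. The ratio of what remains is (1 − 0.366)/(1 − 0.246) = 0.634/0.754 = 0.84.

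**The case against.** **Covariate choice is often left to the analysis plan, and this is a condensed article.** That is a fair limit: no stated figure is wrong here. But the article itself fixes the outcome, the entry floor and the tests, and an analysis plan that follows them inherits the problem.

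**The plan is not purely a comparison of raw means.** This stands. Mann-Whitney U resists outliers, and a repeated measures ANOVA may use the preoperative value. However, no rule says when the rank test replaces the t test, the rank test does not by itself test a mean difference against 12 points, and an ANOVA of AMH levels is on a different scale from the margin.

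**The example is extreme.** It takes patients at the entry floor whose AMH doubles or triples after ovarian surgery. The article does not say how many women will have baselines that low, so domination by such patients is possible but not shown.

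**The precision gain is assumed.** This also stands. The article gives no R², and because the outcome is already divided by baseline, baseline AMH may add little.

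Two stronger readings are tempting and are not supported:

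- A reader might infer that an outlier could produce a false finding of non-inferiority. In these examples it does not: in the experimental arm the inflated SD roughly offsets or nearly offsets the favourable shift, and the limit stays at 7.3 to 8.3, against 8.4 without her.
- A reader might fear a large bias from chance imbalance in laterality. If 30% have bilateral disease (assumed), the SD of the imbalance is √(0.3 × 0.7 × 4/80), about 10 percentage points. That is imbalance in the proportion bilateral, not in AMH decline. If bilateral patients lost 20 points more (assumed), it would mean about 0.10 × 20 = 2 points of decline, which the standard error already allows for.

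**Conclusion.** The point holds as a weakness in the chosen analysis. The outcome is unbounded below, the entry floor permits very small denominators, and one such patient can move an arm mean by 3 to 6 points and inflate its SD. The harm is loss of power and a result that depends on which arm she falls in. Its frequency cannot be stated, because neither the baseline distribution nor the assay error is given.

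Separately, the named tests do not adjust for laterality or hospital, and the two-group tests do not adjust for baseline AMH. Using these covariates costs almost nothing, but the gain to 84–92% power depends on an assumed R² of 0.10 to 0.30 and is not guaranteed.

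The two problems need different remedies, since adjusting the ratio for baseline does not tame its tail.

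**What to change.** Before outcome data are examined, prespecify:

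1. **Primary analysis:** ANCOVA of the 12-week decline ratio on arm, log baseline AMH, laterality and hospital. Non-inferiority is shown if the upper limit of the two-sided 95% CI for experimental minus control is below 12 points. This keeps the outcome and the margin, and replaces the open choice between the t test and the Mann-Whitney test.
2. **Companion analysis for the tail:** ANCOVA of log 12-week AMH on log baseline AMH with the same other covariates. The lower limit of the 95% CI for the geometric mean ratio (experimental to control) is compared with about 0.84. The analysis plan should record that 0.84 translates the 12-point margin at a control decline of 24.6%, and how postoperative values below the assay limit enter the log.

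**Cost:** wording only. Every covariate is already available and no extra patients are needed. The power cost is about 0.04 points with three covariate degrees of freedom, slightly more if further hospitals join. The small downside is a second scale to report.

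Stratifying the randomisation by laterality and hospital is worth considering only if the list is not yet in use. The article anticipated first enrolment in January 2021 and appeared in July 2021, so it may be too late; the two analyses above do not depend on it.

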#### Secondary outcome

The decline ratio of serum AMH levels 48 weeks after surgery.The time required for complete hemostasis: stop-watch will be operated right after finishing to remove EMS tissues. It will be measured how long the time has been spent on bleeding control.Success rates of hemostasis within 10 min: it will be evaluated whether hemostasis is finished within 10 min.Blood loss during operation: the volume of blood loss will be estimated by using a simple visual assessment technique referring to gauze count and irrigation bottle.Hemoglobin: 2 days, 12 weeks, and 48 weeks after surgery.Transfusion during admission.Adverse events associated with the operation, bleeding, or transfusion.Hospitalization (days).Operation time (min).

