### Objectives {7}

This study aims to evaluate the protective effect for preserving the ovarian reserve and hemostasis between a hemostatic agent and suturing during laparoscopic ovarian cystectomy for patients with ovarian EMS. Thus, we will estimate the reduction rate of serum AMH levels for the ovarian reserve, the time required for complete hemostasis, andhemoglobin levels with estimated blood loss for hemostasis between the two methods.

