### Trial design {8}

This is an open-label, parallel-group, randomized controlled, non-inferiority trial. Participants with ovarian EMS will be randomly assigned to the experimental (hemostatic agent) and control (suturing) groups at a 1:1 ratio. After surgical treatment of ovarian EMS, we will check the serum AMH and hemoglobin levels and ovarian volumes measured by transvaginal or transrectal ultrasonography before surgery, after 2 days, after 3 months, and after 12 months. Figure 1 shows the schema of this study.

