## Discussion

Up to now, relevant RCTs have shown no difference in the hemostatic effect between bipolar electrocoagulation and the use of a hemostatic agent [12, 14, 16–18]. This result means that the use of a hemostatic agent can reduce the frequency of use of bipolar electrocoagulation, thereby minimizing thermal damage to the ovarian tissues. In general, the ovarian reserve is defined as the number and quality of the ovarian follicles, and serum AMH levels are known to reflect the ovarian reserve well [9, 19]. Thus, some RCTs have suggested that the use of a hemostatic agent may be more beneficial for preserving the remaining ovarian reserve after laparoscopic ovarian cystectomy by showing that the decline ratio of serum AMH levels was lower in patients treated with a hemostatic agent than in those treated with bipolar electrocoagulation [12, 14, 17].

However, the PRAHA trial showed that the protective effect of a hemostatic agent was observed in only patients with ovarian EMS with no difference in the decline ratio of AMH between the two treatments in those with ovarian non-EMS. It means that the effort to minimize the removal of healthy ovarian tissue and the use of bipolar electrocoagulation can be helpful in preserving the ovarian reserve after laparoscopic ovarian cystectomy in most patients with ovarian cysts. However, we commonly conduct adhesiolysis sufficiently from tissues surrounding the lesion for patients with ovarian EMS. During the procedure, the vascular system within the ovarian cortex or surrounding the ovary can be injured, which can lead to lower serum AMH levels by an inadequate blood supply in the patients [20, 21].

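### Hemoglobin as a hemostasis outcome is listed as raw levels out to 48 weeks and tested without the preoperative value, which costs precision and includes two time points that say little about hemostasis

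*Protocol article*

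**What the plan says.** All references are to the protocol article.

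- Objectives {7} names the measures for the hemostasis part of the aim: "the time required for complete hemostasis, andhemoglobin levels with estimated blood loss for hemostasis between the two methods".
- Outcomes {12}, Secondary outcome, gives hemoglobin as "Hemoglobin: 2 days, 12 weeks, and 48 weeks after surgery". No change from baseline or adjustment is mentioned. The primary AMH outcome, by contrast, is defined relative to its preoperative value.
- A preoperative hemoglobin exists. Under Trial design {8}, "we will check the serum AMH and hemoglobin levels and ovarian volumes measured by transvaginal or transrectal ultrasonography before surgery". The section on biological specimens {33} also places a complete blood count before the operation.
- Statistical methods {20a} assigns Student t or Mann-Whitney tests to numerical secondary endpoints. Repeated-measures ANOVA is mentioned for AMH only.
- Blood loss covers the whole procedure: "Blood loss during operation: the volume of blood loss will be estimated by using a simple visual assessment technique".
- Two other secondary outcomes are confined to the hemostasis step. For the time to complete hemostasis, "stop-watch will be operated right after finishing to remove EMS tissues". Success is judged at 10 min.
- Concomitant care {11d} permits monitored hormonal medication after surgery, and the inclusion criteria require regular menstruation.

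**The concern.** Hemostasis is half of the stated aim, and hemoglobin is its only laboratory measure. Two features of the definition weaken it.

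First, patients differ in hemoglobin before surgery. Comparing raw day-2 levels leaves that spread in the error term, although the value that would remove much of it is already collected.

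Second, the three time points stand on an equal footing. By 12 and 48 weeks, hemoglobin reflects recovery, menstruation and any hormonal treatment rather than control of the ovarian bed months earlier.

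Blood loss has a related weakness. The Discussion notes that "we commonly conduct adhesiolysis sufficiently from tissues surrounding the lesion for patients with ovarian EMS". Bleeding from that dissection and from removing the cyst comes before either hemostatic method is applied, yet it enters the total.

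At stake is how a null result is read. The abstract expects the two methods to be comparable for hemostasis as well as ovarian reserve, and Sample size {14} sets no margin for secondary outcomes. A non-significant difference on an imprecise measure is weak evidence of comparability.

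**Working it through.** **1. Group size.** The only computed figure in the article is the sample size for the primary AMH outcome. With SD 18.81, margin 12, true difference 0, 2.5% taken as one-sided, and 80% power:

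n per group = 2 × (1.960 + 0.842)² × 18.81² / 12² ≈ 38.6, so 39 (78 in total).

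The article has 40 per group (80), so its figure reproduces to within 2 patients. Allowing for 10% dropout, 40 / 0.9 = 44.4, so 45 per group (90), as stated. No size or power is given for any hemostasis outcome, so 40 per group is used below.

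With 40 per group, a two-sided 5% test has 80% power for a standardized difference of (1.960 + 0.842) × √(2/40) ≈ 0.63.

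**2. Day-2 hemoglobin.** The article gives no SD, expected difference or pre-post correlation. Assumed for illustration: SD 1.2 g/dL at both times, a true difference of 0.5 g/dL, and correlation r from 0.3 to 0.8. Power = Φ(difference / (σ√(2/40)) − 1.96), where σ is:

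- raw level: 1.2
- change score: 1.2 × √(2(1 − r))
- ANCOVA: 1.2 × √(1 − r²)

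| r | Raw level | Change score | ANCOVA |
|---|---|---|---|
| 0.3 | 46% | 35% | 50% |
| 0.5 | 46% | 46% | 58% |
| 0.7 | 46% | 67% | 74% |
| 0.8 | 46% | 84% | 87% |

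With ANCOVA the variance is multiplied by 1 − r². At r = 0.5 the factor is 0.75, a 25% reduction. At r = 0.8 it is 0.36, a 64% reduction. This reduction does not depend on the assumed SD or difference. A change score only matches the raw level at r = 0.5 and is worse below that.

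**3. Whole-operation blood loss.** The article gives no variance here either. Assume a true difference of 0.65 SD in loss during the hemostasis step, and independent loss from the rest of the operation with k times the step's SD. Power = Φ(0.65 / (√(1 + k²) × √(2/40)) − 1.96):

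| k | Power |
|---|---|
| 0 (step alone) | 83% |
| 1 | 54% |
| 2 | 26% |
| 3 | 15% |

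The expected difference in mL is the same in every row. Only its precision changes.

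**4. Measurement windows side by side.**

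| Outcome | Window |
|---|---|
| Time to complete hemostasis | Hemostasis step |
| Success within 10 min | Hemostasis step |
| Blood loss | Whole operation |
| Hemoglobin, day 2 | Operation and early recovery |
| Hemoglobin, 12 and 48 weeks | Remote from the operation |

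Day-2 hemoglobin also carries bleeding from before the step. Baseline adjustment removes the spread between patients present before surgery, not that component.

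**The case against.** The strongest reply is that the hemostasis objective does not depend on these measures. Objectives {7} names time to complete hemostasis first. Its stopwatch starts once the cyst is out, and success within 10 min targets the same step. The abstract lists those two among the secondary endpoints and names neither hemoglobin nor blood loss. A reader might infer that hemostasis is judged only on diluted measures and that a real difference is therefore buried. The documents do not support that.

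A reader might also infer bias towards no difference. For example, if 50% to 80% of loss is assumed to precede the step, a 30% reduction in step loss becomes 15% to 6% of the total. That only changes the denominator. Earlier loss is expected to be alike in randomized arms, so the mean difference in mL or g/dL is not shifted. What is lost is precision.

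It can further be said that covariate adjustment of a secondary laboratory value belongs in an analysis plan, and that the article does not exclude it. This has some force and keeps the point modest. But the article does fix the form of the outcome, its three time points and the unadjusted tests, so the remark addresses what is stated.

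The late hemoglobin values are also harmless as follow-up data, which is true provided they are not read as evidence on hemostasis.

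One counterweight remains. The step-specific outcomes are timed in an open-label trial whose operator knows the allocation, and they record speed rather than blood lost. An objective laboratory check is therefore worth making as precise as the data allow.

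**Conclusion.** The point holds as a matter of precision and interpretation in secondary outcomes. Hemoglobin is defined as raw levels and tested without the preoperative value that the trial collects, and two of its three time points have little bearing on intraoperative hemostasis. ANCOVA on day 2 would cut the variance by 25% to 64% if r is 0.5 to 0.8. That range is an assumption, as are the SD, differences and variance ratios behind the power figures; the documents supply none of them. Whole-operation blood loss is less specific than the step-level outcomes, by an amount that cannot be computed from the article.

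No bias is shown, and no real difference is shown to be hidden, because time to complete hemostasis and success within 10 min measure the step directly. The primary non-inferiority conclusion on AMH is unaffected.

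**What to change.** - Define the hemoglobin measure of hemostasis as the day-2 value, analysed by ANCOVA with the preoperative value as covariate. Do not substitute a plain change score.
- Flag transfused patients in that analysis, since transfusion raises the day-2 value. Transfusion during admission is already a listed outcome.
- Report 12- and 48-week hemoglobin descriptively, not as evidence on hemostasis.
- Label whole-operation blood loss as supportive.
- State that the hemostasis conclusion rests mainly on time to complete hemostasis and success within 10 min, and that a non-significant difference on a secondary outcome is not by itself evidence of comparability.

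The cost is outcome and analysis wording only; every value needed is already collected.

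A separate blood-loss reading when the stopwatch starts would isolate the step, but it is a debatable trade-off. It subtracts two visual estimates made by staff who know the allocation, which adds measurement error, so it is not part of this recommendation.

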**Methods:**

This study is a randomized controlled, non-inferiority trial, where a total of 90 patients with ovarian EMS will be randomly assigned to the experimental (hemostatic agent) and control (suturing) groups. In the control group, a barbed suture will be applied for hemostasis, whereas a hemostatic agent will be applied in the experimental group. If two methods are insufficient, bipolar electrocoagulation will be applied for complete hemostasis. As the primary endpoint, the reduction rate of serum anti- Müllerian hormone (AMH) levels reflecting the ovarian reserve will be compared between the two groups 12 weeks after surgery. As secondary endpoints, we will compare the reduction rate of AMH level 48 weeks after surgery, the time required to complete hemostasis, the success rate of hemostasis within 10 min, and adverse events associated with operation.

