### Intervention description {11a}

#### Control group (suturing group)

During operation, a barbed suture will be applied to the inner surface of the ovarian parenchyme where ovarian EMS was attached.

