#### Experimental group (hemostatic agent group)

During laparoscopic ovarian cystectomy, bleeding will be controlled by using a hemostatic agent (EVICEL®, Johnson and Johnson, Republic of Korea), which will be supported by Dalim Medical Corp. (Seoul, Republic of Korea).

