### Assignment of interventions: blinding

#### Who will be blinded {17a}

This item is not applicable because the current research is open-labeled.

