### Adverse event reporting and harms {22}

Adverse events will be collected from the time of intervention to 12 months after the operation. As soon as recognizing the event, relevant investigators will fill them in the electrical case report form in detail. The principal investigator should inform the medical research ethics review committee of this event within 15 days. However, in the current study, interventions conducted in both groups are already done widely during laparoscopic ovarian cystectomy, so that it is expected that there are no additional harms derived from enrollment of this trial. Therefore, all participants get routine hospital care without any specific ancillary and post-trial care.

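### The compared safety outcome keeps only adverse events judged associated with surgery, bleeding or transfusion, in an open-label trial that collects events without that limit; all events should be compared by arm

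*Protocol article*

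**What the plan says.** The list under Secondary outcome gives the safety outcome as "Adverse events associated with the operation, bleeding, or transfusion". The Methods part of the abstract has a shorter form, "adverse events associated with operation".

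The section Adverse event reporting and harms {22} sets a wider collection rule: "Adverse events will be collected from the time of intervention to 12 months after the operation". It puts no relatedness condition on what is collected. On recording, it says that "relevant investigators will fill them in the electrical case report form in detail".

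On blinding, section {17a} states: "This item is not applicable because the current research is open-labeled". Section {16c} adds that the operator and related investigators learn the allocation just before surgery.

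The two interventions are hemostasis methods. In the experimental group, "bleeding will be controlled by using a hemostatic agent"; in the control group, "a barbed suture will be applied to the inner surface of the ovarian parenchyme where ovarian EMS was attached".

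**The concern.** What is collected and what is compared are not the same set. Between them stands a judgement of whether an event is associated with one of three things. The document gives no rule for that judgement and names nobody independent to make it. In an open-label trial such a filter is open to influence from knowledge of the arm, and the influence need not be deliberate.

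The outcome matters for the conclusion the trial is meant to support. The Discussion part of the abstract would prefer the agent for its ease of use if ovarian protection and hemostasis prove comparable. That preference also presumes that harms are no worse, so the harm comparison should be the least discretionary one available.

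Two further points of wording bear on which events count. The factor that is randomised, agent or suture, is not among the named associations. And the opening of the collection window is tied to an undefined moment.

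**Working it through.** The protocol gives no figure for this outcome, so the check is mainly a comparison of its sections.

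**1. Collected against compared.**
- Collected (section {22}): adverse events up to 12 months, with no relatedness limit.
- Compared (Secondary outcome): only those associated with the operation, bleeding or transfusion.
- Difference: events in the window that are judged not associated are recorded but fall outside the named outcome.

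**2. Who applies the filter.**
- Section {17a}: no blinding. Section {16c}: operator and related investigators know the arm before surgery. Section {22}: investigators enter the events.
- No section says who judges association. That it is done by people who know the arm is the natural inference, but it is not stated.

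**3. Are events due to the agent or the suture included?**
- The named associations are operation, bleeding and transfusion.
- The agent and the suture are both applied during the operation, so an event due to either can be read as associated with it.
- An event during the following 12 months that is attributed to the product, and not to the surgery or to bleeding, has no clear place. Two investigators could classify it differently.

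**4. When does the window open?**
- Section {22} opens the window at the intervention and closes it relative to the operation, which are two different words in one sentence.
- The same section describes "interventions conducted in both groups are already done widely during laparoscopic ovarian cystectomy", where interventions are steps within the cystectomy. Section {16b} likewise has patients receive the intervention during the operation.
- The control description places the suture where the endometriosis had been attached, so after excision.
- Read this way, collection would open at hemostasis, and an injury during adhesiolysis or excision would fall before it, although it is plainly an event of the operation. The operator already knows the arm at that stage (section {16c}).
- Read loosely, the intervention is the surgery itself and no gap exists. The text allows both readings.

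**5. Scale of one reclassification.**
- Denominator from Sample size {14}: 40 per arm with 10% dropout, 40/0.9 = 44.4, rounded up to 45 per arm, as stated there.
- One event = 1/45 = 2.2 percentage points.
- Purely hypothetical counts, chosen only to show that the direction is open: agent 7/45 (15.6%), suture 3/45 (6.7%), difference 4/45 = 8.9 points.
  - Three agent-arm events judged not associated: 4/45 against 3/45, difference 1/45 = 2.2 points.
  - Three suture-arm events judged not associated: 7/45 against 0/45, difference 7/45 = 15.6 points.
- The same number of reclassified events can shrink the difference or widen it. Nothing in the protocol says which is more likely.

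**The case against.** The strongest reply is that events associated with the procedure are a recognisable surgical endpoint, and that little is lost here. Section {22} records events without a filter, section {21a} sends adverse events to an independent monitoring committee that meets every six months, and nothing forbids a table of all events. Relatedness scales and safety tables are commonly left to the full protocol or analysis plan. No non-inferiority margin applies to this outcome. The trial is also too small to separate the arms on harms: the hypothetical 7/45 against 3/45 gives a two-sided Fisher p of 0.31.

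Much of this stands. The absence of a relatedness scale or named assessor is not itself the finding, and the abstract's shorter phrase is best read as an abbreviation. What remains is that the protocol does state which events its compared outcome contains, and it states a filtered set. Monitoring by the committee does not change that definition. Low power is a reason for modest claims about harms, not for leaving their counting to discretion.

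Four stronger readings are tempting, and the document does not support them:
- **That reactions to the agent are excluded.** The agent is applied during the operation, so they can be read as included. The suture is not named either, so the wording does not single out the experimental arm.
- **That collection certainly begins at hemostasis.** The starting moment is undefined, and surgery as a whole is a possible reading. The stopwatch rule under Secondary outcome defines a different outcome.
- **That unblinded investigators are the stated judges of association.** They are stated only to record events.
- **That the filter makes the arms look alike.** The direction is undetermined, as the hypothetical counts show.

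Blood loss, transfusion and operation time are separate outcomes and cover part of what happens before hemostasis. They do not record an organ injury as such.

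**Conclusion.** The concern holds as a weakness in how the safety outcome is fixed. The protocol compares a subset of the events it collects, selected by a judgement of association, in a trial without blinding and with no independent assessor named. That can bias the harm comparison in either direction. Whether events attributed only to the agent or suture count, and whether events before hemostasis are collected, is ambiguous rather than settled against inclusion.

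No size of bias can be derived. The only firm figure is that each event counts 2.2 percentage points in an arm of 45. The conclusion assumes that the judgement is made by, or depends on records from, people who know the arm, which follows naturally from the open-label design but is not written down. The primary AMH outcome and the non-inferiority conclusion are not touched. The change is worth making because it is cheap and because the harm comparison bears on whether the agent should be preferred.

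**What to change.** Define the safety outcome as all adverse events and all serious adverse events, by arm and regardless of attribution, from the start of surgery (or from randomisation) to 12 months after it. Report relatedness to the operation, bleeding, transfusion or hemostatic method (agent or suture) as a secondary breakdown. Align the abstract, the Secondary outcome list and section {22}, replacing the undefined starting moment in section {22} with the one chosen.

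The cost is mainly wording in those three places. Events in the current window already go into the case report form. If the window is at present applied only from hemostasis, events during excision must be added, and the form needs to identify serious events and the hemostatic method as a relatedness category if it does not already. The small downside is that unrelated background events add some noise to the comparison; the secondary breakdown lets a reader see how much.
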